## Abstract

**Background:**

Idiopathic sudden sensorineural hearing loss (ISSNHL) is a rapid-onset sensorineural hearing impairment with unclear etiology and unsatisfying treatment effects. Vestibular dysfunction has been considered as a poor indicator in the clinical manifestations and prognosis of ISSNHL, which occurred in approximately 28–57% cases. Glucocorticoids, administered through oral or intratympanic way, are currently regularly and standardly applied for ISSNHL to improve the hearing outcome. However, the vestibular prognosis of ISSNHL after routine treatments remains seldom explored. This study aims to compare the effectiveness of oral and intratympanic glucocorticoids in ISSNHL with vestibular dysfunction in terms of the pattern and trajectory of possible process of vestibular function recovery.

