#### Secondary outcomes

Secondary outcomes include the change of subjective evaluations in vestibular, tinnitus, and hearing assessments:
Change of DHI and VAS-V, VAS-T scores: change of DHI and VAS-V scores from baseline at 1-, 2-, 4-, and 8-week follow-up.Change of PTA: change of average of PTA from baseline at 1-, 2-, 4-, and 8-week follow-up; in this study, we define a 10-dB PTA criterion as clinically significant difference based on a previous RCT [9].Safety: rates of study-related adverse events (AEs), such as short-term systemic use of glucocorticoids related SAEs and AEs, and intratympanic injection-related AEs.

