### Sample size and statistical methods

In our previous studies, we reported the poor indicator of the vestibular system lesion patterns in SSNHL and put forward that the incidence of vestibular dysfunction [30, 31]. However, we only found the existence of vestibular recovery in clinical case reports [16]. Due to lack of previous reported data on changes of vestibular function test results, this study sample size was calculated based on data from preliminary clinical practice in our hospital. Among patients who were diagnosed as ISSNHL and treated with oral prednisone, the recovery proportion of the vestibular function tests (measured by SOT, caloric test, or VEMPs) was 0.25, while the recovery proportion among those treated with intratympanic glucocorticoids was approximate 0.64. Using the program of G*Power 3.1 for Fisher’s exact test, we calculated a sample size of 30 per arm with 80% power at a two-tailed 5% level of significance [32]. To allow for 20% dropout, 36 participants per arm will be needed.

For the outcomes, categoric variables will be expressed as rates, while numerical variables as the mean ± SD. Baseline data will be compared between two groups with a chi-squared test for dichotomous samples and Student’s *t* test or Mann-Whitney *U* test for two independent samples where appropriate. For comparisons of recovery in 4 and 8 weeks from baseline, the recovery rates of vestibular function tests will be calculated by chi-squared tests, and logistic regression adjusts for potential confounders like age, initial PTA, the number of involved vestibular organs, MRI-IAC results, and other characteristics, while the numerical variables like UW of the caloric test, PTA, and scores in DHI, VAS-V, and VAS-T will be calculated by mixed-model with repeated measures analyses of variance (ANOVA), with group and time as fixed effects and subject as a random effect, controlling for the potential confounders. Between two intervention groups, the chi-squared test will be used to analyze the difference for dichotomous outcomes (e.g., recovery rates) and Student’s *t* test for two independent samples or Mann-Whitney *U* test where appropriate. A value of *p* < 0.05 of two-sided is considered statistically significant. We will calculate relative risk (RR) with corresponding 95% confidence intervals to compare dichotomous variables, and mean difference (MD) for continuous variables.

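### The mixed model for the continuous outcomes has no group-by-time term, so as written it gives no treatment effect at any single visit and no difference in trajectory

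*Protocol article*

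**What the plan says.** Under Sample size and statistical methods, the protocol article says that "numerical variables like UW of the caloric test, PTA, and scores in DHI, VAS-V, and VAS-T will be calculated by mixed-model", using repeated-measures ANOVA, and gives the model terms: "with group and time as fixed effects and subject as a random effect", with adjustment for confounders. The sentence opens with its purpose: "For comparisons of recovery in 4 and 8 weeks from baseline". The covariates are "potential confounders like age, initial PTA, the number of involved vestibular organs, MRI-IAC results, and other characteristics". Initial PTA is named. The baseline values of DHI, VAS and UW are not, although the list is open-ended.

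The targets are set elsewhere. Secondary outcomes defines "change of DHI and VAS-V scores from baseline at 1-, 2-, 4-, and 8-week follow-up" and "change of average of PTA from baseline at 1-, 2-, 4-, and 8-week follow-up". The Abstract's Background gives the aim as a comparison of the two routes "in terms of the pattern and trajectory of possible process of vestibular function recovery".

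The methods section also plans t tests or Mann-Whitney tests between the arms, and mean differences for continuous variables. It does not say which visit they use, whether they compare values or changes, or how they rank against the mixed model.

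**The concern.** A model with group and time as separate fixed effects assumes that the difference between arms is the same at every visit in the response. Its single group coefficient cannot show an early benefit that fades, a late one that builds up, or a reversal. The outcomes are defined visit by visit, and the aim speaks of trajectory.

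The mismatch differs a little by outcome. For DHI and VAS-V it is with both the visit-by-visit definition and the aim. For PTA and VAS-T, which are not vestibular measures, it is with the visit-by-visit outcomes only. For UW, which is not listed as a continuous secondary outcome, it is with the aim and with the 4- and 8-week purpose that opens the sentence.

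A second problem depends on how baseline enters. If it is one level of time, the group coefficient also averages in a pre-treatment visit at which randomisation makes the expected difference zero. The estimate is then too small.

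**Working it through.** **The plan's own figure.** The only design figure is 30 per arm, for the binary primary outcome (0.25 versus 0.64, two-sided Fisher's exact test at 5%). Exact enumeration gives power of 79.5% at 29 per arm and 81.9% at 30, so the figure is reproduced. It does not involve the mixed model.

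**Visits, from the protocol article.** DHI and VAS: baseline and weeks 1, 2, 4 and 8, so 5. Caloric test (UW): baseline and weeks 4 and 8, so 3. PTA: 5 under Secondary outcomes and Time points, but baseline, 4 and 8 weeks only under Recruitments and randomization.

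**What the group term estimates.** With complete data, a random subject intercept and no interaction, the group coefficient is the plain mean of the visit-specific group differences over the visits in the response.

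*Baseline in the response, constant effect d after baseline:*
- 5 visits: (0 + d + d + d + d)/5 = 0.8d
- 3 visits: (0 + d + d)/3 = 0.67d

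*Effect at week 8 only:* d/5 = 0.2d and d/3 = 0.33d.

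*Change scores, or follow-up values with a baseline covariate:* a constant effect returns d, with no dilution.

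**Why the average is not enough on either reading.** Assumed differences at weeks 1, 2, 4 and 8 (illustrative, not from the documents):

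| Profile | Group term, baseline in response | Group term, baseline not in response | Difference at week 8 |
|---|---|---|---|
| 0.60, 0.60, 0.60, 0.60 | 0.48 | 0.60 | 0.60 |
| 0.15, 0.30, 0.45, 0.60 | 0.30 | 0.375 | 0.60 |
| 0.60, 0.30, 0, -0.30 | 0.12 | 0.15 | -0.30 |

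In the third row both versions report a small benefit where the arms have crossed. A simulation with 30 per arm, between- and within-patient SD 0.7 and 20,000 runs gave 0.480, 0.300 and 0.119 for the first column, and 0.398 for a constant 0.60 with 3 visits (expected 0.40).

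**UW is less simple.** Time points says that only tests with previously abnormal results are repeated, so a patient with a normal caloric test at baseline has no follow-up UW. Suppose a fraction f of patients have all three visits, the rest contribute baseline only, all stay in the model, and the within-patient correlation is 0.5. The weights are 1/(0.5 + 0.5/3) = 1.5 and 1, and the group term is (1.5f × 0.667d)/(1.5f + 1 - f). That is 0.67d at f = 1, 0.55d at f = 0.75 and 0.40d at f = 0.5. The fraction f is not given.

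**Power, under assumptions only.** Take 30 per arm, SD 1, complete data and correlation r. The standard error is √[(2/30)(r + (1 - r)/k)] for the group term with k visits, and √[(2/30)(1 - r²)] for a week-8 comparison adjusted for baseline. At r = 0.5 these are 0.200 (k = 5), 0.211 (k = 3) and 0.224. For a constant d = 0.7:

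| r | Group term, 5 visits | Group term, 3 visits | Baseline-adjusted week 8 |
|---|---|---|---|
| 0.3 | 90% | 68% | 80% |
| 0.5 | 79% | 59% | 87% |
| 0.7 | 69% | 51% | 96% |

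With 5 visits and r = 0.3 the diluted term has the higher power, because averaging five visits removes noise. An effect at week 8 only (5 visits, r = 0.5) gives about 10%, but nothing in the article predicts that profile. The dilution of the estimate does not depend on r when data are complete. The power loss does.

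**The case against.** The strongest reply is that the article never says baseline is a level of time. The secondary outcomes are defined as changes, and initial PTA is a listed covariate, which for PTA points to baseline-adjusted follow-up values. This stands: the dilution is conditional, and least certain for PTA.

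Second, the clause does not rule out an interaction, and a journal article condenses its full plan. This stands in part. A separate analysis plan may contain the term. But the article does list the model's terms, and that list, followed as written, does not match the outcomes it serves.

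Third, the planned t or Mann-Whitney tests, applied to the change at each visit, would give visit-specific comparisons, and under randomisation a t test of change is unbiased. This also stands in part: the plan as a whole is not confined to the mixed model's group term. But those tests are unadjusted, their visit and scale are not stated, and nothing says which analysis prevails if the two disagree.

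A reader might go further and infer that the model cannot estimate a treatment effect on change at all, or that every continuous result will be biased towards zero. The documents do not support either reading. With change scores or a baseline covariate, the group term does estimate the average effect on change. With baseline in the response it is diluted, not uninformative.

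**Conclusion.** The concern holds in this form. The mixed model as written has no group-by-time term. On any reading of how baseline enters, it yields one averaged group difference, with no visit-specific effect and no comparison of trajectories. That part needs no numerical assumption.

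The dilution to 0.8d (5 visits) or 0.67d (3 complete visits) is exact arithmetic for a constant effect, but applies only if baseline is among the repeated values. That is the natural reading for DHI, VAS and UW, because scores rather than changes are named as the response and their own baselines are not named as covariates. For UW the repeat-only-if-abnormal rule could make it worse. The power figures rest on an assumed effect and correlation and can go either way with 5 visits, so they should not carry the argument.

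A reader might also infer that the trial's main conclusion is at risk. It is not. The primary outcome is a recovery rate analysed by chi-squared tests and logistic regression, and the sample size rests on that outcome alone. Severity is moderate and confined to the secondary and other continuous outcomes.

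**What to change.** For each continuous outcome, model the follow-up values with the outcome's own baseline value as a covariate, and with group, visit and group-by-visit as fixed effects and subject as a random effect. Keep the other pre-stated covariates. Report the group contrast with its confidence interval at each planned visit. State that this model, and not the unadjusted t or Mann-Whitney tests, is the governing between-group analysis.

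The cost is a change of wording and a few parameters: with four follow-up visits the interaction adds three, with two it adds one, and the baseline covariate adds one where it is not already included. The data, visits and software (SPSS) stay the same. Make the change before the analyst is unblinded. It does not cure the UW values that are missing by design, so say which patients that model describes.

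### Two unranked between-arm analyses are planned for the secondary continuous outcomes (DHI, VAS-V, VAS-T, PTA), and neither clearly gives a baseline-adjusted arm contrast at each visit

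*Protocol article*

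**What the plan says.** All of this stands in the protocol article; no separate analysis plan was available.

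- **Outcome definitions** (*Secondary outcomes*). The symptom scores are defined as "change of DHI and VAS-V scores from baseline at 1-, 2-, 4-, and 8-week follow-up". The label of that item also covers VAS-T. PTA is likewise a change from baseline at the same four visits, and "we define a 10-dB PTA criterion as clinically significant difference". No SD is given for any of these measures.
- **Mixed model** (*Sample size and statistical methods*). In a sentence that opens with recovery from baseline at 4 and 8 weeks, "the numerical variables like UW of the caloric test, PTA, and scores in DHI, VAS-V, and VAS-T will be calculated by mixed-model". The model is of the repeated-measures kind, and its terms are given as "with group and time as fixed effects and subject as a random effect, controlling for the potential confounders".
- **Adjusters** (same sentence). They are introduced for the logistic regression as "potential confounders like age, initial PTA, the number of involved vestibular organs, MRI-IAC results, and other characteristics". Initial PTA is named. Baseline DHI, VAS-V and VAS-T are not.
- **Between-group test** (next sentence). It begins "Between two intervention groups, the chi-squared test will be used to analyze the difference for dichotomous outcomes (e.g., recovery rates) and Student’s" and then gives the two-sample t test, or its rank-based Mann-Whitney alternative if that suits the data better, for the other outcomes. No covariate is mentioned. The two-sided 5% rule follows, and then the statement that mean differences will be given for continuous variables.

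**The concern.** The between-group sentence and the mixed-model sentence cover the same continuous outcomes and can give different answers, yet the text does not rank them. Read in order, the first seems to describe change over time and the second to settle the comparison of arms. On that reading the reported arm difference would be an unadjusted two-sample comparison of change, although every one of these measures is collected at baseline.

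Subtracting the baseline is not the same as conditioning on it. A raw change score carries the full baseline noise into the outcome. It also carries any chance difference in baseline means into the estimate: the arm that happens to start worse tends to improve more through regression to the mean. The trial plans about 30 evaluable patients per arm, and the article describes no stratification, so such differences will not be negligible. The *Discussion* expects the intratympanic arm to do better on DHI, VAS-V and PTA, so these contrasts will be interpreted.

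**Working it through.** **Inputs.** From the protocol: 30 evaluable patients per arm, 1:1 allocation, two-sided 5%, a 10-dB PTA difference, and DHI and VAS recorded at baseline and four follow-up visits. Not in the protocol, so assumed: the correlation rho between baseline and follow-up, and the SDs.

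**The plan's own figure.** The 30 per arm was calculated for the binary recovery rate (0.25 against 0.64, Fisher's exact test, 80% power). It reproduces: exact power is 0.819 at 30 per arm and 0.795 at 29. It says nothing about the continuous outcomes, and is used below only as the number of evaluable patients.

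**Variance at one visit.** Let s0 and s1 be the baseline and follow-up SDs.

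- Change score: s1² + s0² − 2·rho·s0·s1
- Follow-up adjusted for baseline (ANCOVA): s1²(1 − rho²)
- Difference: (s0 − rho·s1)², which is never negative

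So, apart from one degree of freedom, adjustment is never less precise. With s0 = s1 the variances are 2(1 − rho) and (1 − rho²) in units of SD². Their ratio is (1 + rho)/2 and the saving is (1 − rho)/2.

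| Assumed rho | Change | ANCOVA | Saving | ANCOVA power where the change-score test has 80% |
|---|---|---|---|---|
| 0.3 | 1.40 | 0.91 | 35% | 93.5% |
| 0.5 | 1.00 | 0.75 | 25% | 89.9% |
| 0.7 | 0.60 | 0.51 | 15% | 86.0% |
| 0.8 | 0.40 | 0.36 | 10% | 84.0% |

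The power column is Φ(2.802/√ratio − 1.96), where 2.802 = 1.960 + 0.842. At rho = 0.5 and 30 per arm, the difference detectable with 80% power falls from 0.72 SD to 0.63 SD.

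The size also depends on the SDs being equal. At rho = 0.5, with s1 = s0/2 the variances are 0.75 and 0.1875 (in s0²), a saving of 75%. With s1 = 2·s0 both are 3, and nothing is saved.

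**Illustration at 10 dB.** With an assumed PTA SD of 20 dB, rho = 0.5 and 30 per arm:

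- Change score: SE = 20 × √(2/30) = 5.16, z = 10/5.16 = 1.94, power 49%.
- ANCOVA: residual SD = 20 × √0.75 = 17.3, SE = 4.47, z = 2.24, power 61%.

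At the same rho, the rise is from 73% to 85% at SD 15 and from 25% to 32% at SD 30.

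**Baseline imbalance.** At equal SDs, a chance difference D in baseline means moves the expected change-score contrast by −(1 − rho)·D. With 30 per arm, the standard error of D is √(2/30) = 0.26 SD. At rho = 0.5 an imbalance of that size shifts the contrast by 0.5 × 0.26 = 0.13 SD.

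**Does the mixed model already supply the adjusted contrast?** Its stated terms are group, time, subject and confounders. If baseline is one of the time levels and there is no group-by-time term, the group coefficient averages over all five visits, including the one before treatment. In balanced data a constant post-treatment effect d then appears as (4/5)d = 0.8d. If baseline is not a time level, it has to enter as a covariate to be used at all, and for DHI, VAS-V and VAS-T that is not stated. Under either reading, a model without the interaction gives one common group effect and not a contrast per visit.

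**The case against.** The strongest reply is that an adjusted analysis of exactly these outcomes is already planned. The mixed model has a group effect and controls for confounders, initial PTA is named among them, and the list is open-ended, so baseline DHI and VAS scores could enter as other characteristics. A journal article may also leave the full covariate list to an analysis plan.

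Much of this stands. A reader might infer that the unadjusted test is the only planned comparison of arms, or that no baseline value is used anywhere. The documents support neither: the mixed model is there, and for PTA its baseline is a named adjuster. Nor is an unlisted covariate a fault in itself.

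What the reply does not remove is that the article fixes a covariate-free test for the between-group comparison and never places the mixed model above it. The model as written also does not clearly yield the adjusted contrast by visit.

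Three further limits are fair. That the two-sample test is applied to change scores is inferred from the outcome definitions, because the test sentence does not say so. The marked early improvement described in the *Discussion* concerns average course and does not establish a low rho. The plan makes no power claim for PTA, so the 10-dB figures only illustrate scale.

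**Conclusion.** The point holds as an improvement to a stated method. Two between-arm analyses compete without ranking. The one named for the comparison of groups uses no baseline covariate, and the other does not name baseline DHI, VAS-V or VAS-T and states no group-by-time term.

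If the two-sample test is run on change scores, the avoidable variance is (1 − rho)/2 at equal SDs, from 35% at rho = 0.3 to 10% at rho = 0.8. A reader might settle on a quarter as the loss. That is only the rho = 0.5 case, and the protocol gives neither a correlation nor an SD. The figure also belongs to a single-visit change-score test and not to the mixed model.

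A reader might also infer that the change-score test is biased or invalid. It is not: under randomisation it is unbiased over repeated trials and keeps its error rate. What is lost is precision, together with robustness of the realised estimate to chance baseline imbalance. All four outcomes are secondary, so the primary outcome and the sample size are untouched.

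**What to change.** In *Sample size and statistical methods*, name one baseline-adjusted arm contrast as decisive for DHI, VAS-V, VAS-T and PTA. Either of these would do:

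- ANCOVA at each visit, with arm and the baseline value of the same measure as covariate.
- The planned mixed model fitted to post-baseline values only, with that baseline as covariate and a group-by-time term, and the arm contrast read off at each visit.

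Report the adjusted mean difference with its 95% CI, and describe the t and Mann-Whitney tests as descriptive.

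The cost is about a sentence of wording and one degree of freedom per outcome for the baseline covariate. In the mixed-model version, the interaction over four follow-up visits adds 4 − 1 = 3 parameters. No new data, visits or patients are needed.

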### Interventions and comparisons

Once a participant is randomized, the treatment procedure starts immediately (Table 1). The participants in group 1 will receive oral prednisone 1 mg/kg/day (maximum daily dosage is no more than 60 mg) for 7 days, followed by a 7-day taper (Table 1). The patients are advised to take the medicine in 30 min before every breakfast, and not to divide the doses. The participants in group 2 will receive 7 intratympanic 40 mg/ml methylprednisolone injections in 14 days, one injection every other day.

**Table 1 Tab1:** Glucocorticoid therapy protocol in each group

	Drug	Protocol
Group 1	Pred.	Glucocorticoid therapy: d1–d7: Oral Pred. 1 mg/kg/d (maximum daily dosage is no more than 60 mg) d8–d9: Oral Pred. 10 mg less than d7 d10–d11: Oral Pred. 10 mg less than d9 d12: Oral Pred. 10 mg less than d11 d13: Oral Pred. 10 mg less than d12 d14: Oral Pred. 10 mg less than d13^a^
Group 2	Met.	Glucocorticoid therapy: One intratympanic injection of 40 mg/ml Met. at d1, d3, d5, d7, d9, d11, and d13;^b^

Pred. prednisone, Met. methylprednisolone, d. day

^a^If the patient’s weight is less than 50 kg, the administration will be stopped after the day with < 10 mg prednisone administered, for example, a patient weighs 45 kg will stop receiving glucocorticoids at the 13th day

^b^One day early or late of injection is allowed for practicality

The otolaryngologists in charge of the injection work are asked to inject at the posterior superior quadrant and fulfill the tympanic cavity using operating microscopes, after lidocaine spray anesthesia. Patients will be asked to keep supine position with the affected ear slightly up to 30° and avoid swallow during injection and in 30 min after the injection. The drug for injection is methylprednisolone sodium succinate for injection by Pfizer Manufacturing Belgium NV.

Of all the participants, the length of treatment would be extended for another week if the change in hearing threshold (average dB in PTA) is less than 10 dB, or average of PTA is worse than 55 dB in the patient’s affected ear, under the participant’s agreement. The salvage treatment regimen is 3 injections of 40 mg/ml methylprednisolone every other day. Records and effects of the salvage treatments will be reported in the study results and evaluated according to both intention-to-treat (ITT) and per-protocol analyses. For those with severe vertigo attacks, drugs for symptom control like mannitol or diazepam can be used temporarily.

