### Adverse events

Any untoward medical occurrences with unfavorable symptoms in the participants are defined as adverse events (AEs). AE is not necessarily to have a causal relationship with the treatment. If the AEs are life-threatening, result in death, persistent, and significant disability or incapacity, or make the participants’ hospitalization, we define them as serious adverse events (SAEs). The investigators will routinely ask the patients if there have been any unexpected symptoms. Study-related and non-study-related AEs will be recorded in the patient’s clinical history by doctors in clinics and then reported to a trial investigator ([name]). Participants experiencing AEs will be followed up until the end of the events or the end of the trial. Any SAEs during this trial will be reported to the trial steering committee (TSC) and Adverse Drug Reaction Administration (ADRA) of the Eye & ENT Hospital of Fudan University within 48 h at learning of the event.

We list some possible study-related AEs here:
Short-term systemic use of glucocorticoids related SAEs: fracture, sepsis, and venous thromboembolism [29];Short-term systemic use of glucocorticoids related AEs: blood glucose problem, appetite change, sleep change, weight change; andIntratympanic injection-related AEs: ear pain, ear infection, tympanic membrane perforation, and worse vertigo after injection.

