### Participant withdrawal

The participants will be informed of the right to withdraw from the study at any time after consent. The enrolled participants who are found ineligible later, lost to follow-up, or withdraw consent for any reason will be regarded as withdrawal. As for those who decided not to receive the protocol intervention, we will ask them if they would like to continue with the follow-up visits and if they agreed, their results will be regarded as variation other than withdrawals in ITT analysis.

We provide an online Wechat and telephone contacts to all the participants for timely communication and health education, which will promote the participants’ retention and adherence to the intervention protocols. Furthermore, we optimized the follow-up process by setting a specialty clinic for SSNHL, minimizing the waiting time, and waiving extra examination and treatment fees.

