An ITT analysis and a per-protocol analysis will be both performed at each outcome. For the missing data in ITT analyses, if there is any, multiple imputation methods will be used. Up-to-date versions of SPSS (SPSS, Chicago, IL, USA) will be used to conduct analyses. A statistician from the Medical College of Fudan University will perform the analyses. Not until the statistician complete the analysis, will he be unblinded to the group allocations and the study hypotheses. All data sent to the analyst will be anonymized, and the study groups will be coded as groups A and B.

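### The ITT and per-protocol rule covers every outcome, safety included, so adverse event rates by randomised arm mix salvage-injection harms into the oral arm and do not describe the initial courses

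*Protocol article*

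**What the plan says.** All references are to the protocol article.

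- **Sample size and statistical methods:** "An ITT analysis and a per-protocol analysis will be both performed at each outcome". On gaps in the data: "For the missing data in ITT analyses, if there is any, multiple imputation methods will be used". Neither sentence is limited to efficacy. The same section plans chi-squared tests and relative risks between groups for dichotomous outcomes.
- **Secondary outcomes:** the list includes "Safety: rates of study-related adverse events (AEs), such as short-term systemic use of glucocorticoids related SAEs and AEs, and intratympanic injection-related AEs".
- **Interventions and comparisons:** salvage is open to both arms. "Of all the participants, the length of treatment would be extended for another week if the change in hearing threshold" is below 10 dB, or the affected ear averages worse than 55 dB, with the participant's agreement. "The salvage treatment regimen is 3 injections of 40 mg/ml methylprednisolone every other day". Salvage records and effects are to be reported and "evaluated according to both intention-to-treat (ITT) and per-protocol analyses".
- **Adverse events:** ear pain, ear infection, perforation and post-injection vertigo are listed separately from systemic steroid effects. "Participants experiencing AEs will be followed up until the end of the events or the end of the trial".
- **Participant withdrawal:** for patients who decline the intervention but stay in follow-up, "their results will be regarded as variation other than withdrawals in ITT analysis". Their place in the per-protocol analysis is not stated, and the per-protocol set is not defined.

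**The concern.** The two analysis sets named are efficacy sets, and the sentence applies them to safety as well. For efficacy, ITT protects the randomised comparison. For harms, a reader also wants to know what happened to people while they were on a given treatment, and neither set answers that here.

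The reason is specific to this trial: the salvage treatment for an oral-arm patient uses the comparator's route. The named injection harms cannot arise from tablets, yet after salvage they would enter the oral arm's AE rate and the relative risk built on it.

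The Background section gives avoidance of most systemic side-effects as one of two reasons for thinking the intratympanic route superior. The AE comparison will therefore be read alongside the efficacy result, even though safety is one of several secondary outcomes and did not drive the sample size.

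**Working it through.** The article gives no safety figure to reproduce. The check is a reading of the sections together, followed by arithmetic on assumed rates. The only plan figure used is 36 patients per arm.

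**Step 1. Does the rule reach safety?** Safety is listed under secondary outcomes, and the rule covers each outcome without exception. Read literally, it does.

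**Step 2. Can salvage AEs arise in the oral arm within the trial?** Salvage is open to all participants and is given by injection. If it follows directly on the 14-day course, it ends at about 14 + 7 = 21 days, well inside the 8-week follow-up. So it can.

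**Step 3. Size in the oral arm under ITT (assumed rates).** Let s be the share of the oral arm taking salvage and r the share of those with an injection AE. The share of the arm carrying such an AE is s × r.

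| s | r | s × r | of 36 patients |
|---|---|---|---|
| 0.2 | 0.1 | 0.02 | 0.7 |
| 0.4 | 0.3 | 0.12 | 4.3 |
| 0.6 | 0.5 | 0.30 | 10.8 |

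Before salvage, this rate is zero in patients who have had only tablets.

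**Step 4. What this does to the between-arm gap in injection AEs.** Salvage can add events in the intratympanic arm too. Let p be that arm's injection-AE rate on the initial course. Assume the same s and r in both arms, and salvage AEs independent of earlier ones.

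- Intratympanic arm: p + (1 − p) × s × r
- Oral arm: s × r
- Gap: p × (1 − s × r)

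With p = 0.3 (assumed), s = 0.4 and r = 0.3, the arms show 0.3 + 0.7 × 0.12 = 0.384 and 0.12. The gap is 0.264, against 0.30 for the initial course alone. Subtracting 0.12 from 0.30 would give 0.18, but that ignores salvage in the intratympanic arm.

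**Step 5. Per-protocol rate (assumed rates and assumed definition).** Let a be the AE rate in the arm and f the share of patients with an AE who stop and are excluded. The per-protocol rate is a(1 − f)/(1 − a × f).

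| a | f | per-protocol rate |
|---|---|---|
| 0.2 | 0.25 | 0.15/0.95 = 15.8% |
| 0.2 | 0.5 | 0.10/0.90 = 11.1% |
| 0.4 | 0.25 | 0.30/0.90 = 33.3% |
| 0.4 | 0.5 | 0.20/0.80 = 25.0% |

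Exclusions unrelated to AEs would leave the expected rate unchanged. The ITT rate keeps all these patients.

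**The case against.** The strongest reply is that a condensed article need not name a safety set, that the analysis plan may do so, and that the methods section discusses only efficacy variables. The absence of a safety set is indeed no finding. The point rests on a sentence that is present and unrestricted, and an analysis plan that adds a treated-patients set would have to depart from it.

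Further replies stand and narrow the point:

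- Salvage belongs to the protocol in both arms, so counting its AEs by randomised arm is a legitimate comparison of strategies. The error would be to read those AEs as effects of oral prednisone.
- Injection-related AEs are a separate category and salvage records will be reported, so such events in the oral arm can be recognised. However, salvage is itself to be evaluated by ITT and per-protocol, not by treatment received.
- Keeping patients who decline treatment in their randomised arm is ordinary ITT.

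A reader might be tempted to infer three stronger things that the document does not support:

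- **That patients who stop for an AE vanish from the safety report.** The per-protocol set is undefined, and the ITT rate, also planned, keeps them.
- **That unobserved AEs will be imputed.** The imputation sentence is unrestricted, but AEs are recorded after routine questioning, and nothing says that an unrecorded AE is treated as a missing value.
- **That the between-arm difference shrinks by the oral arm's salvage-AE rate.** Step 4 shows that this need not follow. For total AEs the gap could even widen, if the oral arm already has more events from systemic effects.

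**Conclusion.** The point holds as a wording fault of low severity. Taken literally, the rule sends the safety outcome through ITT and per-protocol analysis only. Because salvage is by injection in both arms, the resulting AE rates describe strategies that include salvage, not the harms of the initial oral or intratympanic course. A per-protocol AE rate could in addition be too low, if that set is defined in the usual way and some patients stop because of an AE.

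The size cannot be fixed from the article. The ranges of 2% to 30% of the oral arm, and of 11.1% or 15.8% reported where the true rate is 20%, illustrate assumed inputs and are not estimates. The sample size and the efficacy analyses are unaffected.

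**What to change.** In the statistical methods section:

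1. Limit the ITT/per-protocol sentence and the multiple-imputation sentence to the efficacy outcomes.
2. Report observed AEs, without imputation, in all patients who received at least one dose or injection, by initial treatment received.
3. In each arm, tabulate events before and after the first salvage injection separately. This also settles where to place an oral-arm patient who received both routes.
4. Do not use a per-protocol AE rate as the safety result. AE rates by randomised arm may be kept if labelled as a comparison of strategies including salvage.

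The cost is a wording change and one extra table. The salvage and AE records are already to be collected, and no treatment rule or visit changes.
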